### Statistical analysis

Data will be analyzed by using SPSS version 25 software. First, the normal distribution is confirmed by using the Kolmogorov–Smirnov test. If the data are normally distributed, analysis of variance (ANOVA) with repeated measures will be used to compare the mean scores of pain between the groups at different time points. If this is significant, appropriate post hoc tests will be used. A *P* value of less than 0.05 will be considered significant.

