**Methods/Design:**

A randomized clinical trial was designed in compliance with the Consolidated Standards of Reporting Trials (CONSORT). Female students who have moderate to severe primary dysmenorrhea (based on a visual analogue scale [VAS] score of at least 4 for two consecutive months) and who live in dormitories at Qazvin University of Medical Sciences in Qazvin, Iran will be invited to participate in the study. The total sample size will be 88 girls, who will be randomly assigned to intervention (*N* = 44) and control (N = 44) groups. EMDR therapy will be performed for the intervention group, while the control group can use sedative or other pain relife methods as their routin... There will be six treatment sessions, which will be held twice a week. The duration of each session is 30–90 min, according to the convenience of each participant. The data will be collected using the demographic characteristics questionnaire, the VAS, the Subjective Units of Anxiety or Distress Scale (SUD), and the Validity of Cognition Scale (VOC). The data on pain intensity due to primary dysmenorrhea in both groups will be collected at 1 and 2 months before the intervention (to identify eligible participants) and 1 and 2 months after the intervention (follow-ups). Data will be analyzed by using SPSS version 25 software and analysis of variance (ANOVA) with repeated measures with appropriate post hoc tests. A *P* value of less than 0.05 will be considered significant.

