### Sample size calculation

According to previous studies [47, 48], for an effect size of 0.25, power of 0.80, and alpha of 0.05, the sample size is to be 82 subjects (*n* = 41 in each group) using G-Power software. Given the probability of a 10% dropout rate, 44 subjects will be included in each group. The total sample size will be 88 participants.

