### Methods to protect against bias

#### Randomization and allocation

A convenience sampling method will be used for recruitment. The researchers will recruit the female students in dormitories at Qazvin University of Medical Sciences. Eligible participants will be enrolled in the study. They will be randomly assigned to one of two groups by the simple random blocking method with four blocks.

In the block randomization method, the assigning sequence will be written before the commencement of the research. Given that two groups will be studied, four blocks will be used and one letter will be assigned to one group (A: EMDR group; B: control group). All possible modes of the four blocks will be written and numbered as below:1. AABB; 2. ABAB; 3. BBAA; 4. BABA; 5. ABBA; 6. BAAB.

So, in each block, two students will be assigned to the intervention group and two will be assigned to the control group. Then, with a simple random method and the table of random numbers, a number of blocks will be selected from the blocks of numbers. By writing the contents of the blocks for those numbers (as long as the sample size is determined), we will determine the sequence of random allocation. For example, if the numbers are 1, 2, 2, 3, the assigning sequence will be AABB ABAB ABAB BBAA. After the random allocation sequence is generated, it will be numbered from 1 to 88. As a result, every participant will have a unique code.

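### The repeated-measures ANOVA names neither its tested term nor the role of the two screening VAS scores, so the stated 80% power is not tied to an effect at follow-up

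*Protocol article*

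**What the plan says.** The abstract (Methods/Design) places the VAS collections at "1 and 2 months before the intervention (to identify eligible participants) and 1 and 2 months after the intervention (follow-ups"). Under Participants, a VAS of at least 4 in both screening months is required for entry. Study procedure puts randomisation after those two months and the follow-ups at 1 and 2 months after the last session.

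Under Statistical analysis, once normality is confirmed, "analysis of variance (ANOVA) with repeated measures will be used to compare the mean scores of pain between the groups at different time points". A significant result leads to post hoc tests. The section does not say which time points form the time factor, or whether the term of interest is group or group-by-time. It mentions no baseline covariate.

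Under Sample size calculation, "for an effect size of 0.25, power of 0.80, and alpha of 0.05, the sample size is to be 82 subjects", obtained "using G-Power software". The effect metric, test family, number of measurements and correlation are not given. The enrolled number follows from this: "Given the probability of a 10% dropout rate, 44 subjects will be included in each group".

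**The concern.** Two of the four VAS scores precede randomisation, so treatment cannot have affected them and the expected group difference there is zero. If all four enter one time factor and the group main effect is the test, a benefit that exists only at follow-up is averaged with two zeros and halved.

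A repeated-measures ANOVA also gives three tests: group, time and group-by-time. The rule that a significant result opens post hoc tests does not say which of them counts. Because entry requires a high VAS twice, mean VAS may fall in both arms without any treatment effect, so the time effect alone says nothing about EMDR. Two things are at stake: whether the trial has its stated power for the effect it aims to show, and whether the efficacy conclusion rests on a comparison between the randomised groups.

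**Working it through.** **Inputs.** From Sample size calculation: effect size 0.25, power 0.80, alpha 0.05, N = 82. From Randomization and allocation: 1:1 allocation within each block ("two students will be assigned to the intervention group and two will be assigned to the control group"). From the abstract: two VAS scores before and two after the intervention. Assumptions: 0.25 is Cohen's f, which for two equal groups means d = 2f = 0.5; variances are equal; all pairs of occasions share one correlation ρ, taken as 0.5 with range 0.3 to 0.7.

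**Step 1: reproduce N = 82.** For the time-averaged group effect over m measurements, λ = N·m·f²/(1 + (m − 1)ρ), with 1 and N − 2 df. For m = 4 and ρ = 0.5:
- N = 82: λ = 82 × 4 × 0.0625/2.5 = 8.2, power 0.808.
- N = 80: power 0.798.

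The smallest even N is therefore 82. At the same ρ, m = 1, 2, 3 and 5 give 128, 98, 86 and 78.

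**Step 2: is that setting unique?** It is not. The same formula gives 82 for m = 2 with ρ of 0.25 to 0.27, and for m = 3 with ρ of 0.44 to 0.45. A group-by-time interaction over three measurements also gives 82 under the effect-size convention of SPSS output, λ = f²(N − 2)(m − 1). At N = 82, λ = 0.0625 × 80 × 2 = 10 and power is 0.808; at N = 80 it is 0.797.

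**Step 3: power at N = 82 when d = 0.5 at both follow-ups and 0 at both screening months.** For a single-df contrast with mean difference δ and variance v (in SD² units), λ = N·δ²/(4v).

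- *Group effect over four occasions:* δ = (0 + 0 + 0.5 + 0.5)/4 = 0.25 and v = (1 + 3ρ)/4 = 0.625. λ = 82 × 0.0625/2.5 = 2.05.
- *Group effect over the two follow-ups only:* δ = 0.5 and v = (1 + ρ)/2 = 0.75. λ = 82 × 0.25/3 = 6.83.
- *Group-by-time interaction, four occasions, 3 and 240 df:* group differences deviate from their mean by ±0.25, with sum of squares 0.25. λ = (82/4) × 0.25/(1 − ρ) = 10.25.
- *ANCOVA of follow-up mean on screening mean:* δ = 0.5 and residual v = (1 + ρ)/2 − ρ²/((1 + ρ)/2) = 0.75 − 0.25/0.75 = 0.417. λ = 82 × 0.25/1.667 = 12.3.

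| Test | ρ = 0.3 | ρ = 0.5 | ρ = 0.7 |
|---|---|---|---|
| Group effect, four occasions | 0.37 | 0.29 | 0.25 |
| Group effect, two follow-ups | 0.79 | 0.73 | 0.68 |
| Group-by-time, 3 df | 0.60 | 0.76 | 0.95 |
| ANCOVA on screening mean | 0.88 | 0.93 | 0.99 |

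At ρ = 0.5, the four-occasion group effect would need about 316 participants for 80% power, and ANCOVA about 56.

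**Step 4: effect of selection on the ANCOVA figure.** Selecting on VAS of at least 4 in both months narrows the screening scores and weakens their correlation with follow-up. I simulated a normal population with mean 4 to 6, SD 2 to 2.5 and ρ = 0.5 (all assumed). The pre-post correlation between single occasions fell to about 0.31 to 0.39. ANCOVA power for d = 0.5 (in SDs of the selected participants) was about 0.86 to 0.89. The lower end of the ANCOVA row is therefore the more realistic one.

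**The case against.** A reader might infer that all four scores are entered as outcomes and that the 80% claim is therefore false. The text does not support that. Statistical analysis refers only to different time points, and the abstract labels the first two collections as serving eligibility. The match at m = 4 and ρ = 0.5 is suggestive, but Step 2 shows that 82 also arises in other ways. One of them is two follow-ups with ρ about 0.26, and there 80% power does hold for the follow-up effect. Nor can the interaction be ruled out as the basis of 82.

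The effect size is also open. In a between-factors calculation, 0.25 is the time-averaged effect, and 80% holds for that quantity. The 0.29 arises only when 0.25 is taken as the effect at follow-up. The wording on comparing groups at different time points fits the interaction at least as well, and at ρ = 0.5 the loss there is only from 0.80 to 0.76.

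A reader might further infer that falls within each arm will be presented as efficacy. The plan states a comparison between groups, and a concurrent randomised control arm deals with regression to the mean. How large that regression would be depends on population values that the document does not give.

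Finally, repeated-measures ANOVA is a valid randomised comparison, and an article may leave model detail to an analysis plan. All of this stands and limits the claim. It does not remove the point that the stated test and the stated N are not tied to one contrast, and that a better contrast is available from data already to be collected.

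**Conclusion.** The point holds in conditional form. The article commits to a test and to a sample size without fixing the tested term, the role of the pre-randomisation scores or the correlation. Under the reading that reproduces 82 at correlation 0.5 with the four listed collections, power for a follow-up-only d = 0.5 is about 0.29 (0.25 to 0.37). For the interaction or the follow-up-only group effect at correlation 0.5, it is 0.76 or 0.73, a modest shortfall. With two follow-ups and a correlation of about 0.26, there is none.

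These figures rest on reading 0.25 as Cohen's f, on equal correlations between occasions and on 82 completers. The case for changing the analysis does not depend on which reading was intended. Adjusting follow-up VAS for screening VAS gives more power than every listed alternative at each correlation examined, and it leaves no doubt about which effect is tested.

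**What to change.** 1. Make the primary pain analysis the between-group difference in mean VAS over the two follow-ups, adjusted for the mean of the two screening scores. Use ANCOVA, or SPSS MIXED with group, month, group-by-month and baseline VAS, which keeps participants who have only one follow-up.
2. Keep the two screening scores out of the outcome vector.
3. State that the efficacy conclusion rests on this contrast, and not on a time effect or a within-arm change.
4. Restate the sample-size basis for this model, naming the test, the effect metric and the assumed correlation. For d = 0.5 and 82 completers, give the range of about 0.88 to 0.99 for correlations 0.3 to 0.7, and note that selection on VAS favours the lower end. Do not quote 0.93 as a single figure.

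The cost is a rewording of the Statistical analysis and Sample size calculation paragraphs, with the matching sentence in the abstract. No new data, participants or software are needed, and Trial status says that recruitment has not begun.

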### Research aims and hypothesis

The hypothesis is that EMDR therapy can decrease the severity of pain or pain perception in patients with primary dysmenorrhea. The aims are to investigate the effects of EMDR therapy on the intensity of pain, distress level, and validity of cognition.

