### Measures

In this research, four instruments will be used for data collection:

*The demographic characteristics questionnaire* will be used to collect demographic and reproductive characteristics, including age, menarche age, education level, field of study, every menstrual cycle (length of menstrual period and bleeding period), and medication/drug use history. This questionnaire has been developed on the basis of the objectives of the study and its validity will be examined by the content validity method.

*The VAS* will be used to evaluate the severity of dysmenorrhea pain. An Iranian systematic review confirmed the validity and reliability of VAS for evaluation of dysmenorrheal pain [42]. The VAS is a 100-mm line where the “0” end (0) means completely painless and the other end (10) means the most intense pain imaginable. The patient marks the severity of pain on the line. The simplicity makes it easy to use for the assessment of pain [43].

*SUD* is a self-reporting scale with a 0- to 10-point rating scale. Participants are asked to report their level of distress or anxiety based on SUD scale. A score of 0 indicates the absence of distress, and a score of 10 indicates the maximum level of distress [39]. This scale has been widely used by Iranian researchers and its validity and reliability have been confirmed in their studies [44–46].

*The VOC* shows the level of belief in positive or negative recognition. Similar to the SUD scale, it is self-reporting and represents an individual’s assessment of her or his own cognition. A 7-point rating scale ranging from 1 to 7 is used to evaluate, quantify, and indicate the participant’s self-recognition. A score of 1 means a lack of belief in that particular cognition, and a score of 7 means a full belief in it [39]. This scale has been widely used by Iranian researchers and its validity and reliability have been confirmed in their studies [44–46].

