### Primary outcome

The primary outcomes are the pain intensity, anxiety, or distress in patients with primary dysmenorrhea and their cognition of the dysmenorrhea.

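### Three unranked primary outcomes share one unadjusted 0.05 threshold and a sample size set for a single effect, while the hypothesis and the only stated test concern pain alone

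*Protocol article*

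**What the plan says.** The Primary outcome section of the protocol article reads: "The primary outcomes are the pain intensity, anxiety, or distress in patients with primary dysmenorrhea and their cognition of the dysmenorrhea". The Research aims and hypothesis section lists the same three among its aims, to "investigate the effects of EMDR therapy on the intensity of pain, distress level, and validity of cognition". The hypothesis in that section is narrower: "The hypothesis is that EMDR therapy can decrease the severity of pain or pain perception in patients with primary dysmenorrhea".

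The Statistical analysis section names one comparison, a repeated-measures ANOVA to "compare the mean scores of pain between the groups at different time points", followed by post hoc tests if it is significant. It then says that a P "value of less than 0.05 will be considered significant"; the abstract repeats this threshold. The article states no ranking, testing order, adjustment or joint success rule.

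The Sample size calculation section uses one effect size and does not say which outcome it belongs to: "for an effect size of 0.25, power of 0.80, and alpha of 0.05, the sample size is to be 82 subjects".

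Elsewhere the plan is about pain. Eligibility requires a VAS of 4 or more in two successive months (Participants). The follow-up described for both groups is of dysmenorrhea pain, at 1 and 2 months after the last session (Study procedure).

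**The concern.** The article does not settle what would make this a positive trial. Three outcomes have equal standing, one general threshold covers whatever is tested, and the hypothesis and the stated test concern only one of the three.

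The ambiguity has practical weight here. The Intervention section gives the therapy's expected outcome as less subjective distress and a reorganized positive cognition, and SUD and VOC are scored within the sessions, in the desensitization and installation phases. It is a fair inference, though not a documented figure, that these two scales would respond to the sessions more readily than menstrual pain does. The controls receive no intervention and nobody is blinded. A significant SUD or VOC result without a benefit on pain is therefore plausible, and the present list would not prevent its being reported as a positive primary outcome.

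**Working it through.** **1. How many primaries.** Pain is measured by VAS and cognition by VOC. Anxiety and distress are one outcome, because they share one scale (Measures): "Participants are asked to report their level of distress or anxiety based on SUD scale". The count is three, which agrees with the aims.

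**2. Reproducing the planned size.** Inputs from the article:
- effect size 0.25 (read as Cohen's f), power 0.80 and alpha 0.05 (Sample size calculation);
- 1:1 allocation, since in each block "two students will be assigned to the intervention group and two will be assigned to the control group" (Randomization and allocation);
- m = 4 pain measurements, two before and two after the intervention (abstract).

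One input is assumed, because the article does not give it: a correlation between times of rho = 0.5.

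For the between-group test of a repeated-measures ANOVA, lambda = N × f² × m / (1 + (m − 1) × rho), with 1 and N − 2 degrees of freedom.

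At N = 82, lambda = 82 × 0.0625 × 4 / (1 + 3 × 0.5) = 20.5 / 2.5 = 8.2. Power is 0.808, and 82 is the smallest even N that reaches 0.80. The plan's figure is reproduced.

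Other set-ups do not give 82:
- one-way ANOVA: 128;
- three times, rho = 0.5: 86;
- two times, rho = 0.5: 98;
- group-by-time interaction, four times, rho = 0.5: 24.

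The 82 is therefore consistent with one test at the full 0.05.

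**3. Error rate under each reading.**

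*Each outcome is tested at 0.05 and any one success counts.* With independent tests, 1 − 0.95³ = 1 − 0.857375 = 0.1426. Simulation of three equally correlated two-sided z tests (2,000,000 draws per case) gives:

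| Correlation between outcomes | Chance of at least one false positive |
|---|---|
| 0 | 14.3% |
| 0.3 | 13.6% |
| 0.5 | 12.5% |
| 0.7 | 10.9% |
| 0.9 | 8.4% |

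For jointly normal two-sided tests, independence is the worst case. The bound that needs no distributional assumption is 3 × 0.05 = 15%.

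*All three must succeed.* There is no inflation. The cost falls on power: 0.808³ = 0.53 if the outcomes are independent and each has f = 0.25, and more if they are positively correlated.

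*Only pain is tested.* The error is 5%, but SUD and VOC are primary outcomes without a stated analysis.

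**4. Cost of keeping three primaries with control of the error.** The Bonferroni level, which is also the first step of Holm, is 0.05 / 3 = 0.0167. With independent tests the Bonferroni family-wise error is 1 − (1 − 0.0167)³ = 0.049. With the formula and assumptions of step 2:

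| N | Power at 0.05 | Power at 0.0167 |
|---|---|---|
| 82 | 0.81 | 0.66 |
| 88 | 0.83 | 0.70 |

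Power of 0.80 at 0.0167 needs 108 in total before dropout, and 108 / 0.90 = 120 with a 10% allowance. If rho is 0.3 the number before dropout rises from 62 to 84; if rho is 0.7 it rises from 100 to 134. In each case this is roughly a third more.

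**The case against.** A reader might infer that the plan tests all three outcomes at 0.05 and accepts any one as success, so that its false-positive rate is 14%. The article does not support that as a statement of fact:

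- The only test described is of pain. No between-group test of SUD or VOC is written, and the two-group follow-up names pain only. Applying 0.05 to SUD and VOC is read from the general threshold.
- No rule that one success suffices is written. The list of primaries could equally mean that all three must succeed, and then nothing is inflated.
- The 14% is the independence case. Three self-reports about the same menstrual pain are probably correlated, which lowers the figure.
- This is a condensed article. A full analysis plan may exist and may hold a multiplicity rule.

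All four points stand, and they make the inflation conditional. They do not remove the problem. Which outcomes are primary is a protocol decision, and the article has made it in a way that does not match its own hypothesis, follow-up or analysis. The pain-only reading saves the error rate only by leaving two declared primaries without an analysis. Even at a correlation of 0.9, the any-one-counts reading exceeds 5%.

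**Conclusion.** The concern holds in conditional form. The primary outcome is ambiguous: three outcomes are unranked, no success rule is given, one unadjusted 0.05 is stated, and the size was set for one effect. If the threshold is applied to each outcome and any one success counts, the family-wise error is about 8% to 14%, over assumed correlations from 0.9 down to 0. If only pain is tested, the error is 5% and the primary list is wrong. Confidence is high that the list conflicts with the rest of the plan. The size of the inflation is less certain, because it depends on a reading and a correlation that the article does not give. The power figures assume f = 0.25 for each outcome, four times and rho = 0.5.

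**What to change.** Name pain intensity on the VAS as the single primary outcome, tested at 0.05, and say in the sample size section that the effect size refers to pain. This is the outcome of the hypothesis, eligibility, the two-group follow-up and the ANOVA. List SUD and VOC as secondary outcomes without confirmatory claims. Alpha 0.05 and the 82 before dropout then stand, and the repeated-measures analysis need not change for this purpose.

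The cost is a change of wording in the protocol, and in the registry entry if it carries the same list. The small downside is that SUD and VOC lose primary status. The Trial status section says that recruitment has not begun, so the change can precede any data.

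If all three must stay primary, state a Holm adjustment and the analysis of SUD and VOC, and restate the power. At the first-step level it is about 0.66 per outcome at N = 82, not 0.80. Keeping 0.80 at that level needs about 108 before dropout under the same assumptions, so this route costs participants as well as wording.

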### Methods to protect against bias

#### Randomization and allocation

A convenience sampling method will be used for recruitment. The researchers will recruit the female students in dormitories at Qazvin University of Medical Sciences. Eligible participants will be enrolled in the study. They will be randomly assigned to one of two groups by the simple random blocking method with four blocks.

In the block randomization method, the assigning sequence will be written before the commencement of the research. Given that two groups will be studied, four blocks will be used and one letter will be assigned to one group (A: EMDR group; B: control group). All possible modes of the four blocks will be written and numbered as below:1. AABB; 2. ABAB; 3. BBAA; 4. BABA; 5. ABBA; 6. BAAB.

So, in each block, two students will be assigned to the intervention group and two will be assigned to the control group. Then, with a simple random method and the table of random numbers, a number of blocks will be selected from the blocks of numbers. By writing the contents of the blocks for those numbers (as long as the sample size is determined), we will determine the sequence of random allocation. For example, if the numbers are 1, 2, 2, 3, the assigning sequence will be AABB ABAB ABAB BBAA. After the random allocation sequence is generated, it will be numbered from 1 to 88. As a result, every participant will have a unique code.

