### Study procedure

After obtaining permission from the human ethics committee at Qazvin University of Medical Sciences, registering it at the Iranian Clinical Trial Registration Center, and obtaining required permissions from university authorities, the researcher will visit the female dormitories at Qazvin University of Medical Sciences to invite potential participants for this study. There are four dormitories for female students at Qazvin University of Medical Sciences. The researchers will provide the information on the purpose of the research, type of intervention, and confidentiality arrangement for the research data. The participants will be asked to sign the written consent form before enrolling in the study. The researchers also ensure the participants that they can leave the study at any time and can benefit from commonly used palliative treatments whenever they are not willing to continue to participate or when they have severe pain and discomfort related to dysmenorrhea.

During recruitment, potential participants will be initially assessed for the pain intensity related to primary dysmenorrhea monthly for 2 months. Eligible individuals will be randomly assigned to EMDR therapy and control (no intervention) groups by a simple random blocking method with four blocks. EMDR therapy will be performed in the intervention group. The follow-up evaluation of dysmenorrhea pain will be performed in both groups at 1 and 2 months after the last treatment session. The flowchart of the research procedure is presented in Fig. 1.

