#### Allocation concealment

For the purpose of allocation concealment, the name of each group will be written on a card and placed in opaque envelopes; thereby, 88 envelopes will be prepared on the basis of the predetermined sequence. The envelopes are numbered from 1 to 88. Then the envelopes are sequentially opened for every new participant to determine the group.

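### A fixed, published block size of 4 in an unblinded single-university trial makes about one third of allocations deducible in advance, which weakens the envelope concealment

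*Protocol article*

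**What the plan says.** Under Randomization and allocation, the protocol article lists the permitted blocks as "1. AABB; 2. ABAB; 3. BBAA; 4. BABA; 5. ABBA; 6. BAAB" and adds: "So, in each block, two students will be assigned to the intervention group and two will be assigned to the control group". Blocks are drawn at random: "with a simple random method and the table of random numbers, a number of blocks will be selected from the blocks of numbers". The result is a single list: "After the random allocation sequence is generated, it will be numbered from 1 to 88". No other block size and no stratification factor is mentioned.

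On who recruits, the same section says: "The researchers will recruit the female students in dormitories at Qazvin University of Medical Sciences". Recruitment is by convenience sampling, and the Study procedure section describes one university with four dormitories.

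Under Allocation concealment, the group cards go into opaque envelopes numbered 1 to 88. "Then the envelopes are sequentially opened for every new participant to determine the group".

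The Blinding section states that neither participants nor researchers can be blinded. One researcher delivers the EMDR sessions (Intervention) and is also responsible for collecting data (Data management). The outcomes listed as primary are pain, distress and cognition, and the Measures section shows that all three are rated by the participant.

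**The concern.** Opaque envelopes hide the card inside but not the arithmetic of the block. When every block has four places with two per arm, and earlier assignments are visible, the remaining places can be worked out by counting. The block size is printed in the article, the assignments are open, and a single sequence is used up in order, so the count is easy to keep.

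What is at stake is selection at entry. If a recruiter knows that the next envelope holds EMDR, an eligible student who seems keen on the therapy can be brought forward, or a hesitant one can be encouraged less or entered later. The comparison is with no intervention and rests on unblinded self-ratings, so a difference between arms in enthusiasm or expectation could affect the result. The planned repeated-measures ANOVA of pain scores cannot remove a difference in motivation that nobody measured. With blinding ruled out, concealment is the main safeguard at this stage.

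**Working it through.** **Inputs.** The six listed blocks, the two-per-arm rule and the length of 88 come from Randomization and allocation. Equal probability of 1/6 per block is assumed from the simple random selection described there. Open allocation comes from Blinding, and one-by-one opening from Allocation concealment.

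**The plan's own figures.** The number of balanced blocks of size 4 is C(4,2) = 6, the same six as listed. 88/4 = 22 complete blocks, giving 22 × 2 = 44 per arm. Both agree with the article. It states no predictability figure.

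**Allocations certain in advance.** A place is certain once one arm's two places in the block are used up.
- AABB and BBAA: third and fourth places certain, 2 each.
- ABAB, BABA, ABBA and BAAB: fourth place only, 1 each.
- Mean per block: (2 × 2 + 4 × 1)/6 = 8/6 = 1.333.
- Share: 8/24 = 33.3%.
- Over 22 blocks: 22 × 8/6 = 29.3 of 88.
- Minimum 22 × 1 = 22 and maximum 22 × 2 = 44. The count is 22 plus a binomial(22, 1/3) variable, and its central 95% range is 25 to 34.

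**Best-guess accuracy.** The observer guesses the arm with more places left in the block and tosses a coin when they are equal.
- Place 1: 1/2.
- Place 2: 2/3.
- Place 3: (2/3)(1/2) + (1/3)(1) = 2/3.
- Place 4: 1.
- Sum 17/6 per block, so 17/24 = 70.8%, against 50% without blocking.

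**After a change to mixed sizes** (ten blocks of 4 and eight of 6 in random order):
- Total: 10 × 4 + 8 × 6 = 88. Per arm: 10 × 2 + 8 × 3 = 44.
- Certain allocations: lists were simulated against an observer who sees every past allocation and knows both sizes and how many of each there are. The mean is about 6 of 88 (about 7%).
- Best guessing: expected correct guesses are 17/6 per block of 4 and 4.1 per block of 6, so (10 × 17/6 + 8 × 4.1)/88 = 61.13/88 = 69.5%. The simulation agrees.
- Largest interim imbalance: 3 (half of 6) instead of 2 (half of 4).

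One larger fixed size does much less for certainty: a fixed block of 6 leaves 25% certain, and a fixed block of 8 leaves 20%.

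**The case against.** The strongest reply is that a recruiter has little room to use this knowledge. Consent comes first. Two consecutive monthly pain ratings then decide eligibility by a numerical threshold (VAS of at least 4 in both months), and only after that is an envelope opened. Convenience sampling governs who is invited, months before assignment. This largely stands. What is left is the order in which already eligible students are entered and how warmly each is encouraged to go on. It would be nothing if a closed batch of eligible students were randomized together, but the Allocation concealment section describes opening per new participant.

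A second reply is that a steered difference in pain severity would show up in the pre-intervention pain scores. That also stands, and the argument here does not depend on it. It depends on unmeasured motivation, whose effect on the pain outcome cannot be sized from the document.

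A third is that mixed block sizes hardly change guessing: 70.8% becomes 69.5%, about one correct guess fewer in 88. This is true, because asking which arm is behind so far needs no knowledge of the block size. The 50% figure belongs to simple randomization and is not what this remedy achieves.

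Three stronger readings are tempting but unsupported:
- That the envelopes are worthless. On average about 59 of 88 allocations stay uncertain.
- That the team generating the list also recruits with sight of it. The article says only "we will determine the sequence of random allocation". Who holds the list and opens the envelopes is detail that a condensed article may leave to the full protocol.
- That "by a simple random blocking method with four blocks" means a design of four blocks in all. The listed permutations, the two-per-arm rule and the run to 88 show that blocks of size four are meant. It is a slip of wording without consequence.

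**Conclusion.** The concern holds in a limited form. The article fixes a block size that makes one third of allocations deducible on average: 29.3 of 88, never fewer than 22 and never more than 44. This follows from rules that are written down, not from missing detail.

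The conclusion rests on three assumptions: the six blocks are equally likely, someone involved in recruitment tracks earlier assignments, and envelopes are opened one by one as students enter. The article supports the first and third. Open allocation makes the second possible but does not show that it will happen.

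The effect is a weakening of concealment with a narrow route to selection bias. The figures measure predictability and not bias in the pain outcome. It is worth correcting because it is cheap and the outcomes are unblinded self-ratings. It does not by itself invalidate the design.

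**What to change.** Replace the fixed blocks of 4 with a random order of mixed block sizes, for example ten of 4 and eight of 6, and do not disclose the sizes to those who recruit. Leave the sizes out of any text that recruiters see before enrolment closes. While editing, describe the method as permuted blocks of varying size, which also removes the loose reference to four blocks.

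The cost is one new list and 88 refilled envelopes. The Trial status section says that recruitment has not begun, so nothing already done is lost. Sample size and the 44:44 split are unchanged. The price in balance is a possible interim difference of 3 instead of 2. The change should be presented as removing most of the certainty (about 29 down to about 6 of 88) and not as making allocation unguessable.
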